**CONFIDENTIAL**

## 10. STATISTICAL CONSIDERATIONS

### 10.1 Sample Size Considerations

#### Primary indicators:

- The antibody GMT (Omicron) in the experimental group was superior to that in the control group 14 days after immunization.
- H0:  $\delta \leq 0.0212$  vs. H1:  $\delta > 0.0212$  (both are logarithmic scale, equivalent to GMT ratio 95%CI > 1.05)

**Calculating basis for sample size:** by referring to the relevant data of this product in ex-China clinical trials, 0.55 (logarithmic scale) is taken as the standard difference in antibody titer of recombinant COVID-19 vaccine (CHO cell). The probability of type I error  $\alpha=0.025$  (one-sided); power  $1-\beta=0.9$ ; superiority margin  $\Delta=0.0212$  (logarithmic scale, i.e. GMT test group/GMT control group  $\geq 1.05$ ); the test group and the control group are designed according to 1:1.

| Test level
(one sided) | Target     | N of each
group | Superiority
margin         | Actual level
of
difference
between
test group
and control
group | SD          | Total N
after
considering
20% drop-
out |
|---------------------------|------------|--------------------|-------------------------------|-----------------------------------------------------------------------------------|-------------|-----------------------------------------------------|
| 0.025              | 0.9 | 166         | 0.0212
(1.05 fold) | 0.200(
1.6 fold)                                                       | 0.55 | 398                                          |
| 0.025                     | 0.8        | 139                | 0.1139
(1.3)               | 0.30
(2 fold)                                                                  | 0.55        | 348                                                 |
| 0.025                     | 0.85       | 158                | 0.1139
(1.3)               | 0.30                                                                              | 0.55        | 396                                                 |
| 0.025                     | 0.9        | 185                | 0.1139
(1.3)               | 0.30                                                                              | 0.55        | 462                                                 |

CONFIDENTIAL

|       |      |     |                |      |      |      |
|-------|------|-----|----------------|------|------|------|
| 0.025 | 0.8  | 309 | 0.176(
1.5) | 0.30 | 0.55 | 774  |
| 0.025 | 0.85 | 354 | 0.176(
1.5) | 0.30 | 0.55 | 886  |
| 0.025 | 0.9  | 414 | 0.176(
1.5) | 0.30 | 0.55 | 1036 |
| 0.025 | 0.8  | 368 | 0.176(
1.5) | 0.30 | 0.60 | 920  |
| 0.025 | 0.85 | 421 | 0.176(
1.5) | 0.30 | 0.60 | 1054 |
| 0.025 | 0.9  | 493 | 0.176(
1.5) | 0.30 | 0.60 | 1234 |
| 0.025 | 0.8  | 158 | 0.176(
1.5) | 0.35 | 0.55 | 395  |
| 0.025 | 0.85 | 181 | 0.176(
1.5) | 0.35 | 0.55 | 452  |
| 0.025 | 0.9  | 211 | 0.176(
1.5) | 0.35 | 0.55 | 528  |
| 0.025 | 0.8  | 96  | 0.176(
1.5) | 0.40 | 0.55 | 240  |
| 0.025 | 0.85 | 110 | 0.176(
1.5) | 0.40 | 0.55 | 276  |
| 0.025 | 0.9  | 128 | 0.176(
1.5) | 0.40 | 0.55 | 320  |

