**Calculating basis for sample size:**

By referring to the relevant data of this product in ex-China clinical trials, 0.55 (logarithmic scale) is taken as the standard difference of the antibody titer of the recombinant COVID-19 vaccine (CHO cell). The probability of type I error  $\alpha=0.025$  (one-sided); power  $1-\beta = 0.9$ ; non-inferiority threshold  $\Delta=-0.17609$  (logarithmic scale, i.e., the lower bound of 95%

CONFIDENTIAL

confidence interval of GMT test group/GMT control group after immunization should be at least 0.67); The test group and the control group are designed according to 1:1.

| Test level (one sided) | Target     | N of each group | Superiority margin         | Actual level of difference between test group and control group | SD          | Total N after considering 20% drop-out |
|------------------------|------------|-----------------|----------------------------|-----------------------------------------------------------------|-------------|----------------------------------------|
| 0.025           | 0.9 | 206      | -0.17609 (2/3 fold) | 0 (1 fold)                                               | 0.55 | 516                             |
| 0.025                  | 0.9        | 262             | -0.17609 (2/3 fold)        | -0.02 (0.95 fold)                                               | 0.55        | 656                                    |
| 0.025                  | 0.9        | 344             | -0.17609 (2/3 fold)        | -0.02 (0.90 fold)                                               | 0.55        | 860                                    |
| 0.025                  | 0.9        | 566             | -0.17609 (2/3 fold)        | -0.07 (0.85 fold)                                               | 0.55        | 1416                                   |

Based on the above considerations and the drop-out rate, it is planned to enroll 516 participants.

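### The primary sample-size row does not follow from its own inputs: 90% power needs 200 per group and 500 enrolled, not 166 and 398

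*Protocol*

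**What the plan says.** Section 10.1 (Primary indicators) tests superiority of the Omicron GMT at day 14. The text sets one-sided alpha at 0.025 and power at 0.9. For variability, "0.55 (logarithmic scale) is taken as the standard difference in antibody titer of recombinant COVID-19 vaccine (CHO cell"). For allocation, "the test group and the control group are designed according to 1:1".

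The bold row of the superiority table repeats alpha, power and the SD of 0.55. It gives the margin as "0.0212 (1.05 fold") and the assumed true difference as "0.200( 1.6 fold"). Its results are 166 per group and, in the column headed as the total after "considering 20% drop- out", 398. Fifteen further rows follow, with other margins, differences, SDs and powers.

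The second table in the same section covers non-inferiority against the prototype strain. Its bold row gives 206 per group and 516 in total, and the section concludes that "it is planned to enroll 516 participants". In a lower row, the difference column reads "0.02 (0.90 fold"), with a minus sign in front, against 344 per group.

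**The concern.** The bold superiority row is the protocol's only stated power justification for the primary GMT hypothesis, and its n is too small for the inputs printed beside it. The stated n, total and power cannot all be true.

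The row also presents superiority as needing 398 enrolled, so the planned 516 seems to leave 516 − 398 = 118 participants to spare for the primary endpoint. If the real requirement is 500, only 516 − 500 = 16 are spare. Anyone who judged a recruitment shortfall or heavier attrition against 166 or 398 would believe the primary comparison still had 90% power when it did not.

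**Working it through.** **Inputs**, all from Section 10.1, bold superiority row and the text above it: one-sided alpha 0.025 (z = 1.960); power 0.9 (z = 1.2816); SD 0.55; margin 0.0212; true difference 0.200; allocation 1:1; drop-out 20%. The effective difference is 0.200 − 0.0212 = 0.1788.

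**Is the method the protocol's own?** The two-sample t calculation with the printed inputs was applied to the other rows. All 15 other superiority rows agree within one participant per group. Examples:

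| Power | Margin | Difference | SD | Printed n | Recomputed n |
|---|---|---|---|---|---|
| 0.9 | 0.1139 | 0.30 | 0.55 | 185 | 184.5 |
| 0.9 | 0.176 | 0.30 | 0.60 | 493 | 493.0 |
| 0.9 | 0.176 | 0.40 | 0.55 | 128 | 127.7 |
| 0.9 (bold non-inferiority row) | −0.17609 | 0 | 0.55 | 206 | 205.98 |

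**The bold superiority row.** Normal approximation:

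n = 2 × [(1.960 + 1.2816) × 0.55 / 0.1788]² = 198.8, so 199 per group.

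The t calculation gives 199.8, so 200 per group. The protocol prints 166, about 17% too low.

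**Power at given evaluable numbers.** By the normal approximation, power = Φ(0.1788 / (0.55 × √(2/n)) − 1.960). At n = 166 this is Φ(2.962 − 1.960) = Φ(1.002) = 84.2%.

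| Evaluable per group | Origin | Power (normal) | Power (t) |
|---|---|---|---|
| 159 | 398 × 0.8 / 2 | 82.6% | 82.4% |
| 166 | printed | 84.2% | 84.0% |
| 200 | recomputed | 90.2% | 90.0% |
| 206 | 516 × 0.8 / 2 | 91.0% | 90.9% |

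**Could another reading give 166?**
- Taking 1.6-fold exactly (log10 = 0.2041) gives 191.
- Ignoring the margin gives 160.
- One-sided alpha 0.05 gives 163.
- SD 0.50 gives 165.3, so 166. This matches, but contradicts the stated 0.55.

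**Drop-out step.** The other totals equal 2n/0.8 to within 2 participants; for example, 206/0.8 = 257.5, rounded up to 258, and 2 × 258 = 516. For 166 the same rule gives 166/0.8 = 207.5, rounded up to 208, so 416. The printed 398 matches 166 × 2 × 1.2 = 398.4. It also equals 2 × 199, which is the correct normal-approximation n with no drop-out allowance. Neither follows the rule used elsewhere. For 200 per group the rule gives 200/0.8 = 250, so 500.

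**The 344 row of the non-inferiority table.** With SD 0.55 and margin −0.17609:
- a difference of −0.02 gives 261.9, which is the row above (printed 262);
- a difference of −0.04 gives 344.2;
- log10(0.90) = −0.0458 gives 375.2, so 376.

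The printed 344 therefore fits −0.04, which is 10^(−0.04) = 0.912-fold. It fits neither half of its label.

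**The case against.** The arithmetic cannot be answered, but its weight can be argued.

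First, the faulty row does not set enrolment. The correct non-inferiority row does, and at 206 evaluable per group the primary comparison has 90.9% power. Nothing in the protocol makes 166 or 398 a target or a minimum, and no interim analysis is planned. To fall from 258 to 166 evaluable per group, the trial would have to lose about 36% (1 − 166/258), against the 20% allowed for. This stands. The 82% to 84% figures are the power of the printed row, not of the planned trial.

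Second, the cause is not known. SD 0.50 reproduces 166, but so would SD 0.55 with a target power of about 0.84. So would an SD reduced by the planned baseline adjustment, if the correlation between baseline and post-vaccination titre were about 0.41. The protocol gives no such correlation, so that value is purely an assumption. This also stands: SD 0.50 is an inference. The row nevertheless contradicts its own inputs whichever one was changed, and 0.55 appears in the text of both calculations and in the row itself.

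Third, the 344 row is a sensitivity row that determines nothing. That is correct, and it adds no weight to the main point.

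**Conclusion.** The concern holds. By the protocol's own method, the bold superiority row should read 200 per group (199 by the normal approximation) and 500 enrolled. As printed, 166 per group has 84.0% power against the 90% claimed.

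The planned enrolment needs no change. With 516 enrolled and 20% loss, power for Omicron GMT superiority is 90.9%. The fault lies in the stated justification of the primary hypothesis, and its practical effect is to overstate the spare enrolment (118 apparent, 16 actual).

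These figures rest on the protocol's assumptions: common SD 0.55, true log10 difference 0.200, one-sided alpha 0.025 and no gain from covariate adjustment. They concern the GMT comparison only.

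**What to change.** In Section 10.1, bold superiority row, replace 166 by 200 and 398 by 500, keeping SD 0.55 and the division by 0.8 used in the other rows. If a different SD or alpha was really intended, state and justify it, and make the text and the row agree.

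Add one sentence: 516 enrolled, or 206 evaluable per group after 20% drop-out, gives about 91% power for Omicron GMT superiority under the stated assumptions.

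In the non-inferiority table, relabel the 344 row as −0.04 (about 0.91-fold). Alternatively, keep 0.90-fold, change the difference to −0.0458, set n to 376 per group and set the total to 2 × 376/0.8 = 940.

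The cost is a corrected table and one sentence. Enrolment, margins and analysis are unchanged.

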**Secondary indicators:**

The antibody GMT (prototype strain) of the experimental group was not inferior to that of the control group 14 days after immunization.

**Calculating basis for sample size:**

By referring to the relevant data of this product in ex-China clinical trials, 0.55 (logarithmic scale) is taken as the standard difference of the antibody titer of the recombinant COVID-19 vaccine (CHO cell). The probability of type I error  $\alpha=0.025$  (one-sided); power  $1-\beta = 0.9$ ; non-inferiority threshold  $\Delta=-0.17609$  (logarithmic scale, i.e., the lower bound of 95%

CONFIDENTIAL

confidence interval of GMT test group/GMT control group after immunization should be at least 0.67); The test group and the control group are designed according to 1:1.

| Test level (one sided) | Target     | N of each group | Superiority margin         | Actual level of difference between test group and control group | SD          | Total N after considering 20% drop-out |
|------------------------|------------|-----------------|----------------------------|-----------------------------------------------------------------|-------------|----------------------------------------|
| 0.025           | 0.9 | 206      | -0.17609 (2/3 fold) | 0 (1 fold)                                               | 0.55 | 516                             |
| 0.025                  | 0.9        | 262             | -0.17609 (2/3 fold)        | -0.02 (0.95 fold)                                               | 0.55        | 656                                    |
| 0.025                  | 0.9        | 344             | -0.17609 (2/3 fold)        | -0.02 (0.90 fold)                                               | 0.55        | 860                                    |
| 0.025                  | 0.9        | 566             | -0.17609 (2/3 fold)        | -0.07 (0.85 fold)                                               | 0.55        | 1416                                   |

Based on the above considerations and the drop-out rate, it is planned to enroll 516 participants.

## 10.2 Analysis Set

**Full Analysis Set (FAS):** It includes all randomized participants who follow ITT principle, receive 1 dose of vaccine, and have valid immunogenicity data before the first dose.

**Per-Protocol Set (PPS):** It includes all participants who do not violate the inclusion criteria/exclusion criteria, receive 1 dose of vaccine, and have both valid pre- and post-vaccination immunogenicity data. PPS will be defined for immunogenicity evaluations 14 and 28 days after booster vaccination, respectively.

**Immunogenicity Persistence Set (IPS):** It includes the participants who are collected with blood samples at each time point for immunogenicity persistence evaluation and with valid

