### 5.1.3 Criteria for Early Withdrawal from the Trial

Early withdrawal means that the participant fails to complete the booster vaccination and blood collection procedures according to the clinical study protocol and permanently discontinues study participation.

When any of the following conditions occur, the participant will be withdrawn from the study.

- The participant requests to withdraw from the clinical trial;
- Intolerable adverse events, whether related to the investigational drug or not;
- The health status of the participant does not allow them to continue to participate in this trial;
- The participant is vaccinated with other clinical investigational vaccines during the study

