## 7.5 COVID-19 Case Monitoring

This clinical trial adopts a monitoring modality of positive COVID-19 cases with passive monitoring as the main approach and active monitoring as a supplement. After the participants receives the vaccination, the monitoring of positive COVID-19 cases will be initiated until the end of the study, and relevant information will be collected.

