## 7.8 Protocol Violation and Deviation

### 7.8.1 Protocol Violations

The list of protocol violations is as follows (including but not limited to):

- Fail to obtain participant's informed consent;
- Participants who did not meet the inclusion criteria or met the exclusion criteria were enrolled in the study;
- Participants received wrong research interventions (such as incorrect vaccinations);
- Fail to report serious adverse events (SAE) within specified time;
- Received other investigational vaccines during the study period.

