**CONFIDENTIAL**

antibody data. Define the IPS for immunogenicity for 3, 6, 9 and 12 months after booster immunization respectively.

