**Safety Set (SS):**

It includes all participants who receive one dose of booster vaccination. In immunogenicity analysis, the participant who takes the vaccine erroneously will be included as randomized, and the safety data will be analyzed as treated.

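### The persistence set has no rule for titres drawn after infection or a licensed COVID-19 vaccine, and the per-protocol set keeps wrong-vaccine recipients

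*Protocol*

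**What the plan says.** Protocol section 10.2 defines the sets itself.

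- **PPS:** the set is limited to those "who do not violate the inclusion criteria/exclusion criteria, receive 1 dose of vaccine, and have both valid pre- and post-vaccination immunogenicity data". It is formed once for day 14 and once for day 28.
- **IPS:** "It includes the participants who are collected with blood samples at each time point for immunogenicity persistence evaluation and with valid" titre results. One such set is formed for each of the visits at months 3, 6, 9 and 12. Eligibility is not a condition here.
- **Wrong product:** under the Safety Set, "In immunogenicity analysis, the participant who takes the vaccine erroneously will be included as randomized". No exception is made for the PPS or IPS. Section 7.8.1 lists receipt of the wrong intervention as a protocol violation.

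The word 'valid' is not defined. Infection is an exclusion at entry only (section 5.1.2). After vaccination, section 7.5 says "the monitoring of positive COVID-19 cases will be initiated until the end of the study", but no analysis set refers to the cases found. The comparison model in section 10.3.3 contains baseline titre, group and booster vaccination time, and no infection term. Section 10.7 leaves missing persistence data unimputed. On further vaccines, section 5.1.3 gives as a ground for withdrawal: "The participant is vaccinated with other clinical investigational vaccines during the study". Licensed COVID-19 vaccines are not named there.

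**The concern.** Immune persistence is a secondary objective that compares the two boosters over 12 months (section 3.2). Section 2.1 itself notes that people gain immunity from infection as well as from vaccination. A titre drawn after infection therefore does not measure persistence of the booster alone. The trial expects such cases: it monitors them to study end, adjudicates them, and has an exploratory efficacy endpoint. If the better booster prevents more infections, more controls are boosted by infection, and the late ratio moves against the better booster.

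The wrong-vaccine rule is a separate problem with a different mechanism. It mixes in no infection antibody. It puts recipients of the other arm's product into the set meant to hold those treated as planned, and so pulls the arms together. Section 4.4 makes non-inferiority a formal hypothesis, and in such a test dilution of a true difference is not conservative.

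**Working it through.** **The plan's own figure.** Nothing here disputes a stated number. The non-inferiority row in section 10.1 (one-sided alpha 0.025, SD 0.55 log10, margin -0.17609, true difference 0) reproduces: t-test power is 0.8986 at 205 per group and 0.9000 at 206. Then 206 / 0.8 = 257.5, rounded up to 258, and 2 x 258 = 516.

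**Infection: assumptions.** The protocol gives neither an infection rate nor the rise in titre after infection. Let pT and pC be the shares infected before the visit in the test and control arms.

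*Model 1: infection adds a constant b log10 to the titre in either arm.* The ratio is multiplied by 10^((pT - pC) x b).

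| pT vs pC | b = 0.5 | b = 1.0 |
|---|---|---|
| equal | 1.00 | 1.00 |
| 5% vs 10% | 10^(-0.025) = 0.94 | 10^(-0.05) = 0.89 |
| 10% vs 20% | 10^(-0.05) = 0.89 | 10^(-0.10) = 0.79 |
| 15% vs 30% | 10^(-0.075) = 0.84 | 10^(-0.15) = 0.71 |

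*Model 2: infected participants in both arms reach the same level, B = 1 log10 above the control vaccine mean.* With true difference d, the observed difference is (1 - pT) x d + (pT - pC) x B. For illustration d = 0.200, the superiority effect in section 10.1 (ratio 1.58).

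| pT vs pC | Observed log10 difference | Observed ratio |
|---|---|---|
| 5% vs 5% | 0.95 x 0.2 = 0.19 | 1.55 |
| 10% vs 10% | 0.90 x 0.2 = 0.18 | 1.51 |
| 20% vs 20% | 0.80 x 0.2 = 0.16 | 1.45 |
| 5% vs 10% | 0.19 - 0.05 = 0.14 | 1.38 |
| 10% vs 20% | 0.18 - 0.10 = 0.08 | 1.20 |
| 20% vs 40% | 0.16 - 0.20 = -0.04 | 0.91 |

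If d = 0 and the rates are equal, the observed ratio is 1.00 in both models. What remains is extra variance: with a 1 log10 shift in 10% of participants the SD goes from 0.55 to sqrt(0.55^2 + 0.1 x 0.9 x 1^2) = 0.63. The attenuation at equal rates comes from Model 2, where infection overwrites the vaccine difference. Under Model 1 it does not occur.

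**Wrong vaccine.** If a share w is swapped in each arm, the difference becomes d x (1 - 2w).

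- d = 0.2: w = 1% gives 0.196, ratio 1.57; w = 2% gives 0.192, ratio 1.56.
- d = 0, the non-inferiority planning value: no change.
- d = -0.17609, exactly at the margin: w = 1% gives -0.1726, ratio 0.672; w = 2% gives -0.1690, ratio 0.678; the undiluted ratio is 0.667.

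**The case against.** - **Retention after infection is by silence.** Only 'valid' data enter the PPS and IPS, and a statistical analysis plan not shown here could define that word to exclude titres after infection. This stands as a limit: a reader might infer that the protocol chose to keep these titres, and it does not say so. But section 10.2 states the membership rules, and followed exactly they let such titres in. No definition of 'valid' would undo the explicit wrong-vaccine rule.
- **Further COVID-19 vaccines are largely dealt with.** An investigational vaccine leads to withdrawal under section 5.1.3. The sentence on permitted vaccines in section 7.6 is garbled, but neither likely reading permits another COVID-19 vaccine. This stands. The gap is a licensed dose taken all the same, for which no analysis consequence is given.
- **The powered comparisons are hardly exposed to infection.** The sample-size hypotheses are at day 14, and the PPS covers days 14 and 28 with a +10-day window. This stands; the infection point rests on the IPS.
- **The scenarios that show bias assume a difference in infection between arms.** This is fair: the protocol supports no particular rate or direction.
- **Censoring can itself bias.** It conditions on an event after randomisation. If low responders are infected more often, and more controls are infected, censoring removes low-titre controls and raises the control GMT that remains. Monitoring is mainly passive, so undetected infections stay in. Using all samples is a legitimate alternative question. This stands, and is why both analyses are needed.

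**Conclusion.** The point holds in two parts.

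1. **IPS at 3 to 12 months.** As written, it mixes infection-induced with booster-induced antibody. The persistence comparison can be biased if infection differs by arm, and a real difference can be attenuated even when it does not, provided infection brings both arms to a similar level. For assumed rates of 10% vs 20%, the multiplier is 0.89 to 0.79 with a constant boost of 0.5 to 1.0 log10. With equal rates and no true difference there is no bias.
2. **Wrong vaccine in the PPS.** This is an explicit rule that conflicts with the purpose of the set. Its numerical effect is small, about 0.01 to 0.02 on a ratio of 1.58 at 1-2% swaps.

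A reader might go further and infer that the comparisons are biased, the day-14 primary result included. The documents do not support that: they give no infection rates or boost, and the time to day 14 is short. Nor do they support the inference that swaps would materially change the non-inferiority result. The matter should be corrected, but it does not threaten the primary analysis.

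**What to change.** In section 10.2:

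- Limit the as-randomised rule for wrong-vaccine recipients to the FAS, and exclude these participants from the PPS.
- For the IPS, and for the PPS where the effect is small, censor titres from the first PCR-confirmed SARS-CoV-2 infection or the first non-study COVID-19 vaccine onward.
- Report the unrestricted all-samples analysis next to the censored one at each persistence visit, with the number censored per arm.

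The cost is wording; the sample size of 516 does not change. PCR results from symptomatic cases (section 7.5) and prophylactic vaccines (section 7.6) are already recorded. One gap needs a check: the schedule of events ticks concomitant medication only up to the 6-month visit, so vaccination since then may have to be asked about at months 9 and 12. The downside is fewer late samples and possible selection from exclusion after randomisation, with undetected infections remaining; the paired analysis lets the reader see how far the result depends on that choice.
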